**PROTOCOL COVER PAGE**

## REVISION HISTORY

| Revision # | Version Date | Summary of Changes                                                                                                                                                                                                                                                                                                                                                                                                                                                                                                                                                                                                                                                                                                                                                                                                                                                                                                                                                                                                      | Consent Change? |
|------------|--------------|-------------------------------------------------------------------------------------------------------------------------------------------------------------------------------------------------------------------------------------------------------------------------------------------------------------------------------------------------------------------------------------------------------------------------------------------------------------------------------------------------------------------------------------------------------------------------------------------------------------------------------------------------------------------------------------------------------------------------------------------------------------------------------------------------------------------------------------------------------------------------------------------------------------------------------------------------------------------------------------------------------------------------|-----------------|
| 2          | 6/6/2021     | 
 
1. Add COVID-19 vaccine questions to the questionnaire. Previously, we only ask the COVID-19 positive test. With many people received the COVID-19 vaccine, it is important for the study to collect the vaccination status of the participants.
 
2. Clarify the consent language (both English and Hmong) under "What will be done with my data and specimens when this study is over?" so the participants can better understand how the investigators handle the data and specimens.
 
                                                                                                                                                                                                                                                                                                                                                                                                                                                                       | Yes             |
| 3          | 9/23/2021    | 
 
1. Revise the definition of hyperuricemia from 6 mg/dL to 6.8 mg/dL based on the 2020 American College of Rheumatology Guideline for the Management of Gout
 
2. Elaborate the "Word of Mouth" recruitment strategies to include incentives in the recruitment section.
 
3. Revise the study process regarding the collection of medication history, changing "will" to "may" in the following sentence: Participants "may" be asked to bring their medications with them to the enrollment visit and "may" be asked about their adherence to these medicines.
 
4. Update the study flyers in both English and Hmong to include study website and locations where we intend to recruit the participant from.
 
5. Replace the currently used dietary survey to DHQ-3 dietary survey. (DHQ-3 Dietary History Questionnaire is a web-based survey. Therefore, the paper-based DHQ-1, which is similar to DHQ-3, is submitted for review.)
 
 | No              |
| 4          | 11/19/2021   | 
 
1. Revise the consent form on the risk of blood draw. Change the language from "When blood is taken, sometimes people feel a little faint or dizzy for a short time" to, "When blood is taken, sometimes people may faint, feel dizzy or off balance for a short time". The consent form in Hmong does not have the word "feel a little" so the most recent consent form in Hmong has the same meaning as the revised consent form in English.
 
2. Remove the exclusion criteria of "Serum urate measured at enrollment visit > 10 mg/dL", because it is important to include individuals who are at a higher risk of developing gout and study the effect of vitamin C in this population.
 
                                                                                                                                                                                                                                                                | Yes             |

## **ABBREVIATIONS/DEFINITIONS**

- ARDL: Advanced Research and Diagnostic Laboratory
- COVID-19: Coronavirus disease 2019
- CUHCC: Community-University Health Care Center
- DOT: Department of Transportation
- GAQ2.0: Gout Assessment Questionnaire 2.0
- HU: Hyperuricemia
- MCC: Minnesota Community Care
- OHSA: Occupational Safety and Health Administration
- PPE: Personal protective equipment
- SARS-CoV-2: The virus that causes COVID-19
- SU: Serum Urate
- T2DM: Type 2 Diabetes
- ULT: Urate-Lowering Therapy
- UMGC: University of Minnesota Genomics Center
- UMN: University of Minnesota

## 1.0 Objectives

The objectives of this study include:

- Quantify the impact of vitamin C on patient outcomes, including serum urate level, gout-related symptoms, and obesity (measured by BMI) in both healthy Hmong adults and in Hmong patients with hyperuricemia (HU) and/or gout
- Identify associations between individuals' taxonomic and functional patterns of gut microbiota and its impact on the serum urate lowering effect of vitamin C
- Compare taxonomic and functional patterns of gut microbiota between people with HU and/or gout and people without HU and gout
- Identify associations between individuals' taxonomic and functional patterns of gut microbiota and self-reported acute gout trigger foods

Study design is depicted in **Figure 1**.

[figure not shown]

**Figure 1.** Study Design

## 2.0 Background

Gout, caused by chronic elevation of serum urate (SU), is the most common form of inflammatory arthritis worldwide. About 3.9% of adults in the U.S. suffer from gout and prevalence is even higher in certain ethnicities. Factors that may influence SU include patients' characteristics (gender, weight, renal function, etc.), genetics, and diet. Foods and beverages that have shown positive association with HU and gout are alcohol (particularly beer), purine-rich foods, red meat, seafood, and sugar-sweetened drinks, while inverse association has been found with dairy intake such as skimmed milk and low-calorie yoghurt, coffee and vitamin C.

The gut microbiota composition and function have been linked to common chronic human disorders, such as obesity, diabetes, non-alcoholic fatty liver disease, and rheumatoid arthritis. Intestinal microbiota of gout patients were also found highly distinct from healthy individuals in both organismal and functional structures from a small study conducted in China. Strategies to use personal microbiome features to predict glucose response to specific food have been proposed. However, **little is known about the impact of microbiota on food and urate-lowering therapy (ULT)**. The translational significance of a microbiota-guided approach to select appropriate foods and medications that could prevent the elevation of SU for individuals with gout or at high risk for gout is significant.

The Hmong are a unique Asian sub-population. Hmong men exhibit a 2-fold higher prevalence of gout, manifesting it earlier in life and experiencing up to 5-fold increased risk of gout-associated complications, compared to non-Hmong in the US. This could lead to higher rates of cardiometabolic diseases (e.g. hypertension, renal disease, type 2 diabetes [T2DM]), which significantly impact morbidity, mortality and healthcare costs. To prevent acute gout attack and reduce complications associated with gout and/or HU, it is critical to maintain UA below 6 mg/dL.

In this study, we will test four hypotheses and thereby accomplish our objectives as following:

**Ho (1):** High dose vitamin C intervention improves outcomes in (a) healthy adults and (b) patients with HU and/or gout.

Rationale: Previous studies had demonstrated vitamin C 500 mg twice daily for 8 weeks is effective in lowering serum urate compared to placebo in healthy adults. However, one study in patients with gout receiving vitamin 500 mg once daily for 8 weeks did not find significant serum urate reduction in patients on allopurinol.

We will test this Ho1 (a) and (b) by giving vitamin C 500 mg twice daily to all the study participants and analyze by 3 groups: 1) participants with HU and/or gout with ULT, 2) participants with HU and/or gout without ULT, and 3) participants without HU and gout.

The outcome measures include both biological surrogate marker (serum urate), patient reported outcome (gout-related symptoms), and obesity (measured by BMI).

**Ho (2):** The urate-lowering effect by vitamin C is influenced by gut microbiome.

Rationale: Humans cannot produce their own vitamin C; therefore, dietary is an important source of vitamin C. However, recent computational analysis identified *Burkholderia*, *Pseudomonas* and *Erwinia* possessed the machinery to produce ascorbate. These genera are commonly seen in patients with Crohn's disease. The presence of these organisms can impact the production of the anti-inflammatory ascorbate metabolite. This could have an impact on the treatment effect (most likely the anti-inflammatory effect) of vitamin C in patients with gout.

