### **3.0 Study Endpoints/Events/Outcomes**

3.1 Primary Endpoint/Event/Outcome: Absolute change in serum urate after the 8 week of vitamin C intervention

3.2 Secondary Endpoint(s)/Event(s)/Outcome(s): Secondary outcomes include the followings:

- Change in gout related symptoms measured by Gout Assessment Questionnaire 2.0^15 and number of joints affected by gout using Swollen Joint Count (44 Joints) post-administration of vitamin C
- Change in BMI
- Taxonomic and functional patterns of gut microbiota associated with SU
- Change in taxonomic and functional patterns of gut microbiota post-administration of vitamin C
- Taxonomic and functional patterns of gut microbiota associated with food types that trigger gout

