## 5.0 Procedures Involved

- 5.1 Study Design: This is an open-label interventional study. We aim to enroll 2:1 matching between participants with HU and/ or gout and participants without HU and gout. We aim to have 3 analysis groups of about 60 people per group (total about 180 participants): 1) people with HU or gout with ULT, 2) people with HU or gout without ULT, 3) people without HU or gout without ULT.

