#### 15.2 Power Analysis:

For an effect size of 0.5 mg/dL SU reduction from baseline by vitamin C, using a one-sided *t*-test, 80% power, type 1 error of 0.01, and 15% drop-out rate, 120 in adults with HU and/or gout (standard deviation, SD of 1.5 mg/dL) and 60 adults without HU and gout (SD of 1 mg/dL) are required.

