#### 15.3 Statistical Analysis:

Absolute SU changes from baseline to week 8 will be calculated using multiple linear regression adjusting for patients' characteristics including age, gender, BMI, renal function, and concomitant medications. Genetic variants and microbiome features will be tested with forward stepwise regression.

Overall differences in microbiome composition from baseline to week 8 will be compared using three principle axes of variation in the microbiome. A linear regression will be analyzed with a bacterial taxon as dependent and host factors as independent variables. The significance of association of a host factor will be determined by the test of the null hypothesis that the coefficient is equal to zero. For microbiome features, we will correct computed p-values for the total number of comparisons between dependent and independent variables using false discovery rate correction.

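### The serum-urate hypothesis is powered on two populations but analysed in three groups, and no deciding contrast is named; each urate-lowering-therapy group has only about 50% power

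*Protocol*

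**What the plan says.** The protocol describes the test of Ho1 in five places.

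- **Hypothesis (2.0).** It has two parts: "High dose vitamin C intervention improves outcomes in (a) healthy adults and (b) patients with HU and/or gout".
- **How it will be tested (2.0, rationale for Ho1).** All participants receive vitamin C, and the investigators will "analyze by 3 groups: 1) participants with HU and/or gout with ULT, 2) participants with HU and/or gout without ULT", with participants without HU or gout as the third group. The same rationale lists as outcome measures serum urate (SU), "patient reported outcome (gout-related symptoms), and obesity (measured by BMI").
- **Design (5.1).** "We aim to have 3 analysis groups of about 60 people per group (total about 180 participants"), with HU/gout again split by ULT.
- **Endpoint (3.1, 3.2).** The primary endpoint is "Absolute change in serum urate after the 8 week of vitamin C intervention", with no population named. Gout symptoms, swollen joint count and BMI are secondary.
- **Power and analysis (15.2, 15.3).** The power statement begins "For an effect size of 0.5 mg/dL SU reduction from baseline by vitamin C" and uses a one-sided t-test with "80% power, type 1 error of 0.01, and 15% drop-out rate". It gives 120 adults with HU and/or gout (SD 1.5 mg/dL) and 60 without (SD 1 mg/dL). The analysis is: "Absolute SU changes from baseline to week 8 will be calculated using multiple linear regression adjusting for patients' characteristics", followed by a list of covariates. It names no group term, contrast or significance level. The false discovery rate correction is given for microbiome features only.

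**The concern.** The two-part hypothesis and the power statement point to one test in pooled HU/gout and one in participants without it. The rationale for Ho1 and section 5.1 point to three tests. Section 15.3, read literally, is one regression that specifies neither. A later analysis plan could supply the missing contrast, but whichever it chose, it would have to depart from either the three groups or the two sized populations.

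Two things are at stake.

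1. **Power.** If part (b) is judged separately with and without ULT, the planned 80% does not apply to those tests.
2. **Choice after the data.** The pooled and split analyses of part (b) can give different answers from the same data. The protocol itself gives reason to expect groups to differ: it cites urate lowering in healthy adults and no significant reduction in patients on allopurinol, the latter at a lower daily dose. In an open-label study with no named contrast, the reading of part (b) could be settled after results are seen.

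**Working it through.** **Inputs**

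- Effect 0.5 mg/dL within group, one-sided 0.01, 80% power, 15% drop-out (15.2).
- SD 1.5 (HU/gout) and 1.0 (without), with enrolment of 120 and 60 (15.2).
- Groups of about 60 (5.1).
- Completers: 120 × 0.85 = 102; 60 × 0.85 = 51.
- Assumption: SD 1.5 also applies within each ULT group. The protocol gives no separate figure.

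**Step 1: the plan's own sample size.** The smallest n with 80% power in a one-sample t-test on the change, from the noncentral t, is:

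- HU/gout: 94 evaluable; 94 / 0.85 = 110.6, so 111 (stated 120).
- Without HU/gout: 43 evaluable; 43 / 0.85 = 50.6, so 51 (stated 60).

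The stated numbers are not reproduced. They are larger than needed, so the difference is in the safe direction and is not part of this point.

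**Step 2: power of each candidate test.** Noncentrality = (0.5 / SD) × √n; power = P(noncentral t with n − 1 df > t₀.₉₉).

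| Group | n | SD | Noncentrality | Critical t | Power |
|---|---|---|---|---|---|
| HU/gout pooled | 102 | 1.5 | 3.367 | 2.364 | 84.0% |
| Without HU/gout | 51 | 1.0 | 3.571 | 2.403 | 87.4% |
| HU/gout with ULT | 51 | 1.5 | 2.380 | 2.403 | 49.6% |
| HU/gout without ULT | 51 | 1.5 | 2.380 | 2.403 | 49.6% |

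For 80% power, each ULT group would need the 111 of step 1, not 60.

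**Step 3: can the choice change the answer?** For illustration only, suppose the true fall is 0.5 mg/dL without ULT and 0 with ULT. The pooled mean fall is then (0.5 + 0) / 2 = 0.25. Pooled noncentrality is (0.25 / 1.5) × √102 = 1.683, which gives power of about 25%. The group without ULT keeps about 50%.

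**Step 4: error rate across tests.** This step assumes that any one positive test would count as support for Ho1, that each test is run at one-sided 0.01, and that no group has an effect.

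- Two populations: 1 − 0.99² = 0.0199.
- Three groups: 1 − 0.99³ = 0.0297.
- Three groups plus pooled HU/gout: 0.034, by simulation of 4,000,000 draws, because the pooled test overlaps two of the groups.

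**The case against.** **Inflation of the type 1 error.** A reader might infer that the true false-positive rate for Ho1 is two to nearly four times the stated 0.01. The documents do not support that as a fact. The protocol has no rule that one positive test suffices. If parts (a) and (b) are separate claims about separate populations, each keeps 0.01. If both must succeed, the error is at most 0.01. The 0.01 is stated only for the two populations in 15.2, not for the ULT groups or the regression. Nor is a test in all participants listed anywhere as a test of Ho1. What stands is the conditional range of 2.0% to 3.4%.

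**Symptoms and BMI.** A reader might also infer that Ho1 could be declared on these, because the rationale lists them beside SU. Section 3.2 already ranks them as secondary, so they should not be counted as further primary tests. One clarifying sentence is enough.

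**Different answers for (a) and (b).** These would not be an error. They are different populations, and how often they disagreed would mostly reflect the effects assumed.

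**Left to an analysis plan.** Marginal means, the exact coefficient and any multiplicity procedure commonly sit there, and the adjustment for concomitant medications may cover ULT. That is fair, and the absence of those details is not the point here. The mismatch between two sized populations and three analysed groups remains within the protocol.

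**Conclusion.** The point holds as an internal inconsistency. Section 15.2 powers Ho1 on two populations, the rationale in 2.0 and section 5.1 analyse three groups, and 3.1 and 15.3 do not say which result decides. If Ho1 is tested as the rationale says, each HU/gout ULT group has about 50% power for 0.5 mg/dL, against 84% pooled and 87% without HU/gout.

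These figures rest on the protocol's effect, SDs, significance level and drop-out, on a one-sample t-test of the change, and on SD 1.5 within each ULT group. The conclusion that 80% does not cover the ULT groups needs nothing further. The 2.0% to 3.4% chance of at least one false positive also needs a decision rule that the protocol does not state, so it is a reason to write the rule down and not a measured fault.

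**What to change.** - **Sections 3.1 and 15.3, with matching wording in the Ho1 rationale and 5.1.** Name two primary contrasts: mean week-8 SU change in pooled HU/gout, for part (b), and in participants without HU or gout, for part (a). State that each is a separate claim tested at the one-sided 0.01 of section 15.2.
- **ULT groups.** Report the with-ULT and without-ULT groups as secondary estimates with confidence intervals, and state that each has roughly 50% power for 0.5 mg/dL.
- **Outcomes.** State that Ho1 is decided on SU, and keep gout symptoms, joint count and BMI secondary as in 3.2.
- **Optional.** If the sponsor wants one overall 0.01 across (a) and (b), Holm is affordable. Power at 0.005 is 76.9% (pooled) and 80.9% (without HU/gout). With independent groups, Holm gives 0.769 + (0.840 − 0.769) × 0.809 = 0.826, about 83%, for (b), and 0.809 + (0.874 − 0.809) × 0.769 = 0.859, about 86%, for (a). Both stay above 80%.

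The cost is wording only, with no extra participants or data. The downside is that the ULT groups lose stand-alone confirmatory status.

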We will test this Ho3 by comparing the taxonomic and functional patterns of gut microbiota of those with HU/gout (with or without ULT) to those without HU or gout.

**Ho (4):** Food types that trigger gout can be predicted by individuals' taxonomic and functional patterns of gut microbiota.

Rationale: There is a strong correlation between an individual's taxonomic patterns of gut microbiota and self-reported trigger foods in patients with type 2 diabetes. The correlation could also be present in patients with HU and gout.

We will test this Ho4 by comparing the taxonomic patterns of gut microbiota of individuals with gout who have similar self-identified trigger foods to those who have different trigger foods.

### **3.0 Study Endpoints/Events/Outcomes**

3.1 Primary Endpoint/Event/Outcome: Absolute change in serum urate after the 8 week of vitamin C intervention

3.2 Secondary Endpoint(s)/Event(s)/Outcome(s): Secondary outcomes include the followings:

- Change in gout related symptoms measured by Gout Assessment Questionnaire 2.0^15 and number of joints affected by gout using Swollen Joint Count (44 Joints) post-administration of vitamin C
- Change in BMI
- Taxonomic and functional patterns of gut microbiota associated with SU
- Change in taxonomic and functional patterns of gut microbiota post-administration of vitamin C
- Taxonomic and functional patterns of gut microbiota associated with food types that trigger gout

### **4.0 Study Intervention(s)/Investigational Agent(s)**

4.1 Description:

All participants will be taking vitamin C 500 mg twice daily by mouth for 8 weeks. All participants will continue taking their prescribed medications during the study period.

Vitamin C is commercially available over-the-counter food supplements. Vitamin C will be purchased from a GMP manufacturer (such as Pure Encapsulations, Sudbury, MA) which can demonstrate a good quality and safety of the product.

4.2 Drug/Device Handling:

The vitamin C will be stored securely in a locked cabinet at [name] office. Vitamin C is an over-the-counter product and will be distributed by research staff as per applicable regulations. The label will list the name of the study, the number and frequency of tablets to be taken, the participant's name and ID number, and the phone number for a pharmacy helpline. A study dispensing and accountability log will be maintained by bilingual research staff. The participants will be reminded to return the study pill containers and any remaining tablets at Week 8.

- 4.3 Biosafety: This study does NOT involve recombinant or synthetic nucleic acid molecules (r/sNA; RNA, DNA), infectious agents, or biologically-derived toxins.
- 4.4 Stem Cells: This study does NOT involve embryos or embryonic stem cells.
- 4.5 Fetal Tissue: This study does NOT involve human fetal tissue or cell lines derived from human fetal tissue.

## 5.0 Procedures Involved

- 5.1 Study Design: This is an open-label interventional study. We aim to enroll 2:1 matching between participants with HU and/ or gout and participants without HU and gout. We aim to have 3 analysis groups of about 60 people per group (total about 180 participants): 1) people with HU or gout with ULT, 2) people with HU or gout without ULT, 3) people without HU or gout without ULT.

